**Study assessment and procedures**

**Screening visit**

During screening visit will be obtained written informed consent, patients medical history collection and treatment (antiretroviral or not) with complete registration of all concomitant medications, the search for markers of HBV and HCV infection, pregnancy test for women of childbearing age or serum FSH dose for women in menopause for less than 2 years, complete physical examination of vital signs, weight and height, blood tests (liver and kidney function, fasting glucose, complete lipid profile, amylase, Na, K, P , Ca, Cl, CK, uric acid), complete blood count, complete urinalysis, lymphocyte immunophenotyping, HIV-RNA. Will also be determined the genotypic tropism of HIV-V3 from viral DNA extracted from whole blood by sequencing.

**Baseline**

The day the simplified therapy with maraviroc, darunavir / ritonavir will be administered for the first time will be defined as baseline (day 0); in the control group the baseline will be represented by the first visit after the randomization . The physical examination should be repeated along with the determination of vital signs, weight and height, blood tests (liver function, including ALT, AST, tot bil / alkaline phosphate and gammagt, and kidney, fasting glucose, complete lipid profile, amylase, lipase, Na, K, P, Ca, CK), the complete blood count, urine examination complete, the lymphocyte immunophenotyping, HIV-RNA, and set aside a plasma sample and a sample of whole blood for 'genotype analysis of V3 on RNA and DNA, respectively. Furthermore, additional analysis will be performed on the bone metabolism (alkaline phosphatase, calcitonin, parathyroid hormone, osteocalcin, dose of vitamin D3, urinary hydroxyproline, urinary hydrossiploline).

Renal function is monitored by calculation of the CG or MDRD and the measured creatinine clearance, 24 hours proteinuria, natriuria, Kaliuria, calciuria, phosphaturia, chlorides and uricuria 24 hours.
Fasting insulin levels will also be assessed at baseline. In specific subgroups subcutaneous fat on the face, arm and thigh will be measured by ultrasound (Liposound); the average intima media thickness (IMT), carotid Doppler ultrasound, endothelial function by flow-mediated dilation (FMD) of brachial artery and bone mineral density and distribution of subcutaneous fat by DEXA will also be measured.

Finally, patients will be asked to complete a self-reported adherence questionnaire, a self-reported questionnaire on symptoms and quality of life and will undergo an evaluation of basic neurocognitive screening tests, and if necessary based on the screening tests, a more in depth evaluation using extensive neurocognitive assessment batteries. On the same day candidates will be subjected to the patients randomized 1:1 in the following arms:

A) * Maraviroc 300 mg (1 tablet) every 24 h + 800 mg darunavir (2 400 mg tabs) every 24 h + ritonavir 100 mg (1 heat stable tablet) every 24 h in the morning (in order to make TDM)
B) Continuation of previously ongoing treatment

* 150 mg (1 tablet) every 24 h if estimated creatinine clearance <80 ml ​​/ min

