**Study design**

This is a 2-arm, prospective, multicenter, open- label, 1:1 randomized controlled trial. The number of patients planned to be included is 330 (165 per arm). The expected duration of the study include 6 months for enrollment, 28 days of screening at baseline, 96 weeks of treatment (48 weeks for the primary endpoint) and 30 days of follow-up after the end of the study. In case of virological failure (defined as the occurrence of 2 consecutive HIV-RNA above 50 copies / mL or a single value greater than 1000 copies / mL) therapy will be modified guided by resistance genotype and discontinuation of the CCR5 antagonist; in case of no genotyping for low levels of viremia (or other technical reasons) the new regimen will include at least one PI / r associated with drugs selected on the basis of best clinical judgment.

Drugs will be distributed by outpatients structures and batch and expiration date of each package of medication delivered will be recorded.

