**Secondary Endpoints**

• proportion of patients with virological failure (two consecutive measures of HIV-RNA higher than 50 copies/mL or a single measure higher than 1000 copies/mL) within 96 weeks at intention-to treat analysis with missing value=failure.

• time to virological failure at survival analysis

• proportion of patients with X4 viral tropism at failure (RNA or DNA genotyping)

• proportion of patients with at failure X4viral tropism at failure (RNA or DNA genotyping)

• economic impact of DRV/r+ MVC versus current ART

• modification of IMT and FMD from baseline at 48 and 96 weeks

• modification of bone density from baseline at 48 and 96 weeks

• evolution of CD4 cell count during the 96 study weeks

• modification of metabolic parameters during 96 weeks

• modification of the results of neurocognitive tests from baseline at 48 and 96 weeks

• evolution of maraviroc plasma concentrations during the 96 weeks

• evolution of adherence and quality of life after 24, 48 and 96 weeks

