DEXA for bone densitometry, body fat evaluation and IMT will be performed at selected centers among the sites participating. These procedures do not lead to additional costs for the structure.
The concomitant therapy will be verified by the study doctor at each visit, any changes to existing treatment at the screening visit recorded in the monitoring visits will be recorded.

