**STUDY ASSESSMENT AND PROCEDURES**

**Flow-chart/Time and Events Schedule**

| **Procedures** | **Screening**  **(day -28)** | **Basale**  **(giorno 0)** | **Follow-up visit (weeks 4, 12, 36)** | **Follow-up visit (week**  **24)** | **Follow-up visit (week 48)** | **Follow-up visit**  **(week s**  **60, 72, 84)** | **Follow-up visit ( week 96)** | **Follow –up vist post-treatment**  **(after 30 days)** |
| --- | --- | --- | --- | --- | --- | --- | --- | --- |
| Written informed consent | **X** |  |  |  |  |  |  |  |
| Medical history | **X** |  |  |  |  |  |  |  |
| Therapeutic history | **X** |  |  |  |  |  |  |  |
| Concomitant medication use | **X** | **X** | **X** | **X** | **X** | **X** | **X** | **X** |
| HBsAg ed anti-HCV | **X** |  |  |  |  |  |  |  |
| Serum pregnancy test or serum FSH | **X** |  |  |  |  |  |  |  |
| Full physical examination, vital signs, height, weight | **X** | **X** | **X** | **X** | **X** | **X** | **X** | **X** |
| Blood exam and urine analysis | **X** | **X** | **X** | **X** | **X** | **X** | **X** | **X** |
| Urine analysis (24 hours) |  | **X** |  | **X** | **X** | **X****** | **X** |  |
| Hematology chemistry | **X** | **X** | **X** | **X** | **X** | **X** | **X** | **X** |
| Lymphocyte subsets and HIV RNA | **X** | **X** | **X** | **X** | **X** | **X** | **X** | **X** |
| Darunavir, ritonavir and maraviroc TDM (arm a)*** |  |  | **X** | **X** | **X** | **X** | **X** | **X** |
| Whole blood sample for viral DNA genotyping | **x** | **X** | **X** | **x** | **x** | **x** | **x** |  |
| Blood sample for HIV resistance test ant tropism test | **(*)** | **(*)** | **(*)** | **(*)** | **(*)** | **(*)** | **(*)** |  |
| Fasting insulin, study of bone metabolism |  | **X** |  | **X** | **X** | **X** | **X** |  |
| **IMT, FMD, body fat |  | **X** |  |  | **X** |  | **X** |  |
| **Bone DEXA |  | **X** |  |  | **X** |  | **X** |  |
| Adherence self-reported questionnaire |  | **X** | **X** | **X** | **X** | **X** | **X** |  |
| Symptoms questionnaire and QoL |  | **X** | **X (only week 4)** | **X** | **X** | **X** | **X** |  |
| **Neurocognitive test |  | **X** |  |  | **X** |  | **X** |  |

(*) sample storage at -20°C and for analysis in virological failure (two consecutive measures of HIV-RNA higher than 50 copies/mL or a single measure higher than 1000 copies/mL)

** in selected participating centers

*** TDM in 20 patients at week 4 with 9 points of determination **** at week 72

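### IMT and FMD are secondary endpoints of an open-label trial, but nothing keeps the ultrasound operator unaware of the arm, and the plan is inconsistent on who is scanned and whether baseline scans precede allocation

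*Combined protocol and SAP*

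**What the plan says.** The Study design section describes a "2-arm, prospective, multicenter, open- label, 1:1 randomized controlled trial". The Secondary Endpoints section lists "modification of IMT and FMD from baseline at 48 and 96 weeks". Ultrasound measurement of subcutaneous fat is scheduled but is not on that list.

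Three places say who is measured:

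- Baseline section: "In specific subgroups subcutaneous fat on the face, arm and thigh will be measured by ultrasound (Liposound"). IMT, FMD and DEXA follow in the same sentence after a semicolon. The subgroups are not defined.
- Monitoring section: "DEXA for bone densitometry, body fat evaluation and IMT will be performed at selected centers among the sites participating". FMD is not named here.
- Flow chart: the rows for IMT, FMD and body fat, for DEXA and for neurocognitive testing carry the footnote "in selected participating centers". The scheduled times (baseline, weeks 48 and 96) are not split by arm.

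On timing, the Baseline section says that "in the control group the baseline will be represented by the first visit after the randomization". After setting out the baseline assessments, the same section says "On the same day candidates will be subjected to the patients randomized 1:1 in the following arms".

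The available text mentions no masked operator, no masked or central reading, and no rule that a patient stays with one machine or operator.

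**The concern.** IMT and FMD readings depend on where the probe is placed and which image the operator accepts. An operator who knows the arm can, without intending to, read the two arms differently. That route is open at weeks 48 and 96 however the measured subset is chosen.

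There is a second, weaker route. If the decision to scan a patient is made once the arm is known, and no rule fixes who is scanned, the measured patients in the two arms may not be comparable.

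At stake is how far a vascular difference between arms can be believed. IMT and FMD are the listed vascular measures, and a difference in either direction would be open to the objection that the operators knew the treatment.

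**Working it through.** The plan gives no subset size, standard deviation, target effect or power for IMT or FMD, so it has no figure to reproduce. The check is a comparison of the text, followed by an illustration on assumed inputs.

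**1. Who is measured.** The Baseline section restricts by subgroup of patients; the Monitoring section and the flow chart restrict by centre. These are different rules. They agree only if the subgroups are simply the patients at the selected centres, which is not stated. No text names the centres, says how they are selected, or says that every patient at such a centre is scanned. The subgroup wording attaches most directly to ultrasound fat; whether it also governs IMT and FMD is unclear.

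**2. When the baseline scan happens.** The control-arm baseline is defined as a visit that follows randomisation. The arm A baseline is the day of the first dose of the simplified regimen, which must also follow allocation. Yet the section lists the assessments, ends with questionnaires and neurocognitive tests, and only then describes randomisation on that same day, which suggests assessments first. The two statements cannot both fix the order.

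**3. What the operator knows.** Treatment is open-label, and nothing in the available text withholds the arm from the person scanning at baseline, week 48 or week 96.

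**4. What a reading shift could do.** All inputs here are assumptions: m patients per arm measured, and a shift of b SD of the change score in one arm only, with no true difference. A constant reading habit cancels in change from baseline, so b is the part of the shift that differs both by arm and between visits.

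- SE of the difference in mean change = sqrt(2/m), in SD units.
- Error rate = Φ(b/SE − 1.96) + Φ(−b/SE − 1.96).

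| Per arm (m) | SE | b = 0.1 | b = 0.2 | b = 0.3 |
|---|---|---|---|---|
| 20 | 0.316 | 6.2% | 9.7% | 15.8% |
| 40 | 0.224 | 7.3% | 14.5% | 26.9% |
| 80 | 0.158 | 9.7% | 24.4% | 47.5% |

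For example, with m = 40 and b = 0.3, b/SE = 0.3/0.224 = 1.34, and the error rate is 26.9%. For a fixed shift, a larger subset makes the error rate worse.

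The table assumes a between-arm test of change. The statistical section names independent-sample tests at baseline and paired tests for change, so it does not clearly state such a test.

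**The case against.** The subset can be read as defined by centre. Two places say so, and the flow chart gives both arms the same visits. If every patient at those centres is scanned, selection is by site and not by arm. The order of the text in the Baseline section also suggests scanning before randomisation. Subcutaneous fat, to which the subgroup wording attaches, is not a listed endpoint. IMT and FMD form one of twelve secondary bullets, and the primary endpoint is a laboratory viral load. No size of bias can be taken from the documents.

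Most of this stands and sets the limits of the point. A reader might infer that the plan lets sites pick patients by arm. The documents do not support that: they leave it possible through an undefined subgroup and an unclear order, but they do not provide for it. A reader might also infer that any resulting bias is beyond repair. That goes too far: counts by arm and visit, with a comparison of baseline characteristics, would help expose selection, and if images are kept (the documents do not say) a masked re-read could address reading bias.

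The reading route is not answered. Even if all patients at the selected centres are scanned, and scanned before allocation, operators at weeks 48 and 96 may still know the arm.

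**Conclusion.** The point holds in a limited form. In an open-label trial with IMT and FMD change as a secondary endpoint, the plan does not keep the operator unaware of the arm. It contradicts itself on whether baseline scans precede allocation, and it gives two unreconciled rules for who is measured. Reading that depends on the arm is an open risk; selection that depends on the arm is a gap in the text and not a stated rule.

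The size is hypothetical. The range of about 6% to 48%, against a nominal 5%, rests on an assumed 20 to 80 patients per arm, an assumed arm-specific shift of 0.1 to 0.3 SD, and a between-arm test of change that the plan does not clearly specify. The HIV-RNA primary endpoint and the sample size are not touched. This is a cheap improvement to how secondary data are collected, not a threat to the trial's main conclusion.

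**What to change.** - Reconcile the Baseline section with the Monitoring section and the flow chart: every consenting patient at a selected centre is measured, and the centres are named.
- Amend the Baseline section so that baseline IMT, FMD and body-fat scans are completed before allocation is revealed in both arms. This must include the definition of the control-arm baseline for these measures, which at present falls after randomisation; otherwise the contradiction remains.
- State that operators are not told the arm at baseline, week 48 or week 96: requests omit it, and patients are asked not to disclose it. Use the same machine for each patient and, where possible, the same operator at all three visits.
- Report the numbers measured by arm and visit.
- In the same edit, add FMD to the repeat measurements and to the selected-centre sentence in the Monitoring section. It is a listed endpoint and is in the flow chart, but both of those places omit it.

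The cost is a change to the protocol text, site instructions and minor scheduling effort, using existing operators and machines. Operator masking will be imperfect because patients know their treatment, so it reduces the risk but does not remove it.

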
**Objectives**

The specific goals of the study are

1. to verify the virological non-inferiority after 48 weeks of the treatment simplification from a "standard" combination antiretroviral therapy including 3 drugs to Maraviroc (MVC) plus Darunavir/ritonavir QD, in patients virosuppressed from 24 weeks showing any grade toxicities to ongoing treatment or willing to reduce drug or need to simplify therapy or NRTI sparing regimen
2. to collect relevant information about the safety, the immunologic and the economic impact of this strategy

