**Eligible subjects**

• males and females >/= 18 years of age

• HIV infected with R5 tropism by viral DNA genotyping (geno2pheno "clonal")

• treated with the same HAART regimen including 3 drugs from at least 4 months

• with at least two viral load < 50 copies/mL in two consecutive determinations at least 6 months apart (tolerance of two weeks)

• with CD4 cell count > 200 cells/μL and without any opportunistic infection or AIDS-related disease for at least one year prior to the screening

• who gave informed consent to the participation to the study.

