**Non eligible subjects**

• With at least one major or two minor mutations conferring resistance to darunavir reported in the update list of International AIDS Society - USA , in previous resistance tests. Previous determination of D/M or X4 viral tropism

• Previous major clinical toxicities (grade >=3) to the proposed drugs of the study

• Pregnancy or breast feeding, desire of pregnancy in the short term

• Past exposure to CCR5 antagonist

• HBsAg positive serostatus

• Liver cirrhosis of class C (Child-Pugh)

• Sulpha drug hypersensitivity

• The presence of major non AIDS-defining diseases that, in the opinion of the investigator, may compromise the retention of the patient in the study for the necessary follow-up period.

• Estimated glomerular filtration < 30 ml/min (Cockroft-Gaut; MDRD if black-African or african-american) at screening visit

•Hypertransaminemia of grade IV (more than 10 times the upper normal limit) at screening visit

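### Patients may enter on any three-drug regimen, including one built on darunavir/r, but the plan does not stratify, adjust or report by entry regimen

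*Combined protocol and SAP*

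**What the plan says.** Eligible subjects requires that a patient be "treated with the same HAART regimen including 3 drugs from at least 4 months". No drug or class is named. Non eligible subjects bars patients "With at least one major or two minor mutations conferring resistance to darunavir" and those with "Past exposure to CCR5 antagonist", together with earlier toxicity of grade 3 or higher to the study drugs and sulpha hypersensitivity. It does not bar current darunavir/r use. That such patients may enter follows from the absence of an exclusion; no sentence says so outright.

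Under Baseline, arm A receives maraviroc with "800 mg darunavir (2 400 mg tabs) every 24 h + ritonavir 100 mg (1 heat stable tablet) every 24 h", and arm B is "B) Continuation of previously ongoing treatment". Study design states "This is a 2-arm, prospective, multicenter, open- label, 1:1 randomized controlled trial" and gives no stratification factor or allocation method. Statistical analysis and sample size calculation assumes one control success rate of 90%. It lists per-protocol, observed and intention-to-treat analyses, and mentions no regimen stratum, covariate or subgroup. For laboratory measures it offers independent-sample tests at baseline and paired tests of change.

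Antiretroviral treatment is recorded at the screening visit, so the classifying variable exists for every patient before randomisation.

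**The concern.** The randomised comparison contains two contrasts. A patient already on darunavir/r plus two other drugs who is allocated to arm A keeps the anchor drug and exchanges the rest for maraviroc. A patient on another third drug also starts darunavir/r. Under Primary Endpoint, stopping or adding a drug counts as failure in either arm, so tolerability of newly started drugs can enter the primary outcome. So can tolerability of retained drugs, because Objectives admits patients "showing any grade toxicities to ongoing treatment or willing to reduce drug". Both may vary with the entry regimen.

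The same holds for secondary endpoints such as "modification of bone density from baseline at 48 and 96 weeks", metabolic parameters and cost, which plausibly depend on which drugs the control patients keep. At stake is interpretation: a clinician will ask whether the result applies to a patient already on darunavir/r, to one who is not, or to both, and the plan prespecifies nothing that addresses this.

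**Working it through.** **Plan's sample size.** Inputs from the statistical section: 90% success (taken as equal in both arms, since no experimental rate is stated), margin 10 points, two-sided 95% interval, 80% power, 5% lost.

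- Unrestricted variance: n = 2 × 0.09 × (1.960 + 0.842)² / 0.10² = 141.3, so 142; 142 / 0.95 gives 150.
- Farrington–Manning (variance restricted under the null; restricted rates about 0.931 and 0.831): n = [(1.960 × 0.452 + 0.842 × 0.424) / 0.10]² ≈ 154.5, so 155; 155 / 0.95 gives 164, close to the stated 165.

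The plan does not name its formula. Below, 165 × 0.95 = 156.75 is taken as 156 evaluable per arm.

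**What one pooled figure can hide.** Let w be the share entering on darunavir/r (not given; assumed), with deficits D1 in these patients and D2 in the rest. Pooled deficit = w × D1 + (1 − w) × D2. At w = 50%, a pooled deficit of 5 points results from each of these:

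| D1 (on darunavir/r) | D2 (others) | Pooled |
|---|---|---|
| 5 | 5 | 5 |
| 0 | 10 | 5 |
| 10 | 0 | 5 |

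The pooled analysis cannot tell these apart.

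**Chance of declaring non-inferiority if D1 = 0 and D2 = 10.** With control success 0.90 and experimental success p = 0.90 − 0.10 × (1 − w), the chance is Φ[(0.10 − pooled deficit) / SE − 1.96], where SE = √[(0.09 + p(1 − p)) / 156].

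| w | Pooled deficit | Chance |
|---|---|---|
| 0% | 10 | 2.5% |
| 20% | 8 | 7.4% |
| 40% | 6 | 18.3% |

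Exact enumeration at 157 per arm gives 2.7%, 7.9% and 19.3%.

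**Bias and type I error of the pooled comparison.** Simulation used simple randomisation, 156 per arm, w of 30% or 50%, assumed control success of 95% on darunavir/r and 85% to 87.9% otherwise, and a true pooled deficit of 10 points. The mean estimate was −10.0 points and non-inferiority was declared in 2.7% to 2.9% of trials. There is no between-arm bias.

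**Chance imbalance.** The 95% range of the between-arm difference in share is 1.96 × √[2w(1 − w)/n]. At w = 30%, n = 156: 1.96 × √(0.42/156) = 10.2 points. With an assumed 10-point prognostic gap between regimens, the risk difference moves by 0.102 × 10 ≈ 1.0 point; with a 5-point gap, by 0.5.

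Bone density and IMT/FMD are measured at selected centres only. Their numbers are not stated. Assuming 50 or 30 per arm and a regimen type held by half the patients, the range is 1.96 × √(0.5/50) = 19.6 or 1.96 × √(0.5/30) = 25.3 points of share.

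**Precision by class.** Half-width = 1.96 × √(2 × 0.09/m), with m patients per arm in the class. For 50% of patients (m = 78) it is 9.4 points; for 30% (m ≈ 47), 12.2 points. The difference between two classes of 78 per arm has half-width √(9.4² + 9.4²) = 13.3 points.

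**The case against.** The strongest reply is that the pooled effect is the question asked. Objectives concerns simplification from a standard three-drug combination, and the statistical section tests against maintaining the current regimen. A control arm that continues treatment answers that question. This stands.

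A reader might infer from the second table that darunavir/r users push a failing strategy inside the margin and so inflate false positives. The documents do not support that reading, for two reasons. If the true pooled deficit is 6 points, declaring non-inferiority at a 10-point margin is correct, so the percentages are ordinary power. They also rest on an assumed zero difference in darunavir/r users, for which there is no evidence in the plan. Background and Rationale cites a pilot in untreated patients, not powered for non-inferiority, with the same boosted PI in both arms and maraviroc against two NRTIs: 80% against 89% were suppressed at 24 weeks. It used another PI and another population, but it does not suggest that keeping the PI removes the difference. The masking could run either way.

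A reader might also infer that the regimen mix is uncontrolled between arms, or that the lipid results come from a small substudy. Randomisation balances the mix in expectation, and lipids are measured at every monitoring visit. Nor can allocation be called simple, since the method is not stated. Some pages are withheld from the public text, so a stratification statement there cannot be excluded, although the sections where it would belong have none.

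Finally, the exclusions for earlier severe toxicity to the study drugs and for sulpha hypersensitivity limit start-up intolerance. They reduce the contrast between the two kinds of patient but do not remove it.

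**Conclusion.** The point holds as a gap in prespecification. It does not threaten the validity of the trial. The pooled estimate is unbiased, its type I error is close to nominal, and chance imbalance in regimen costs the primary comparison about 1 point or less under the assumed gaps. The remaining weakness is that one figure covers patients who keep darunavir/r and patients who start it, with no planned estimate to show whether it fits both. How much this matters depends on the share entering on darunavir/r and on regimen-specific effects, neither of which the documents give.

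Imbalance in share can be larger for bone density and IMT/FMD, but its effect on those outcomes cannot be sized from the plan, and the 30 to 50 per arm used above is an assumption.

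It would be going too far to rest the conclusion for patients not on darunavir/r on their own stratum. With 94 per arm in that stratum (60% of 156) and 90% success in both arms, the half-width is 1.96 × √(0.18/94) = 8.6 points, and power is Φ(0.10/0.0438 − 1.96) ≈ 63%.

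**What to change.** - **Randomisation.** Stratify the 1:1 allocation by screening regimen: already on darunavir/r; other boosted PI; no boosted PI. If enrolment has started, use these classes in the analysis only.
- **Primary analysis.** Estimate the 48-week risk difference as a stratum-weighted difference (for example with Mantel–Haenszel weights) and its 95% interval. The non-inferiority conclusion rests on this pooled figure.
- **By class.** Prespecify the 48-week difference with 95% interval in each class and label it descriptive.
- **Secondary endpoints.** Name a between-arm model for lipids, bone density and IMT/FMD, with regimen class and baseline value as covariates. The present text gives only baseline comparisons and paired tests.

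The cost is a slightly more complex randomisation list and a few sentences in the statistical section. No new data are collected and 165 per arm stands. The plan should say openly that by-class intervals will be imprecise and cannot reliably separate a 10-point difference between classes.
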